#### 7.1.3 Other study parameters (if applicable)

Possible moderators of main study parameter:

- number and recency of previous depressive episodes
- age of onset first depressive episode
- life events and childhood trauma
- personality

Possible confounders/mediators:

- amount of rumination
- baseline and change in negative affect

### 7.2 Randomisation, blinding and treatment allocation

Subjects are randomized to MBCT + treatment as usual (experimental group) or treatment as usual (control group). Randomization takes place after the baseline measurements and first week of ESM. This is because ESM measurements are not

considered valid in case <30% of the responses are valid. Subjects that have not enough valid ESM response are excluded from the study before randomization. Subjects are obviously not blind to their treatment allocation, however, they do remain blind as to how ESM measures relate to testing the hypothesis.

### 7.3 Study procedures

First, subjects are screened for the participation criteria and fill in a questionnaire concerning demographic variables.

At baseline subjects:

- undergo Psychiatric interviews: SCID-I and the Hamilton Depression Rating Scale (HAM-17).
- fill in some questionnaires concerning depressive symptoms (SCL-90), personality (NEO-PI) rumination (RRS), life events (Interview for Recent Life Events) and early adversity (Childhood Trauma Questionnaire)
- spit some saliva in special tubes as to measure polymorphisms/haplotypes in the DNA that have been associated in previous studies with the brain reward system. (Since insights concerning relevant polymorphisms and haplotypes change rapidly, an up-to-date relational (i.e. cross-relating genotype, phenotypic expressions, biochemical pathways) database relevant for the neurosciences is maintained within our department. Genetic analyses thus are always matched against the most recent information).
- participate in the 6-day ESM period as described under 'study design'. Subjects will be briefed and de-briefed before and after the ESM period, respectively.

Subjects randomized to the experimental group will participate in an 8-week-period of MBCT, including weekly sessions of 2,5 hours in which the training takes place and daily homework exercises. They also fill in to what degree they complied with the homework exercises every day (in minutes).

After the intervention, subjects from both groups (experimental and control) again undergo the psychiatric interviews and the questionnaires.

In addition, they participate in another 6-day ESM period and are again briefed and de-briefed with respect to this procedure. The ESM debriefing includes the collection of the diaries and discussion concerning unclarities or missing values.

### 7.4 Withdrawal of individual subjects

Subjects can leave the study at any time for any reason if they wish to do so without any consequences. The investigator can decide to withdraw a subject from the study for urgent medical reasons.

#### 7.4.1 Specific criteria for withdrawal (if applicable)

Not applicable

### **7.5 Replacement of individual subjects after withdrawal**

In case subjects withdraw before randomization, they will be replaced. After randomization they will not be replaced. The power calculation takes into account a certain amount of drop-out from the study.

### **7.6 Follow-up of subjects withdrawn from treatment**

Subjects that withdraw from treatment will be asked the reason of withdrawal. In addition, it will be examined whether these subjects differ in any characteristics from those that do not withdraw.

### **7.7 Premature termination of the study**

Not applicable

*< Please describe the criteria for terminating the study prematurely and the procedures in case the study will be terminated prematurely.>*

## **8 SAFETY REPORTING**

Not applicable

## **9 STATISTICAL ANALYSIS**

### **9.1 Descriptive statistics**

Frequency tables and chi-square tests are used for categorical data and means and standard deviations for continuous variables.

### **9.2 Univariate analysis**

Analyses are corrected for possible confounders, thus only multivariate analyses will be used.

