## 3. STUDY DESIGN

### ***Experience Sampling Method***

ESM is a structured diary, momentary assessment technique to study subjects in their daily life. Subjects receive a diary, containing a set of ESM self-assessment forms (rated on 7-point Likert scales) and a digital watch. Ten times a day on six consecutive days, the watch emits a signal at unpredictable moments between 7.30 a.m. and 10.30 p.m. To assess positive affect in responses to environmental situations, reports of current context (activity, persons present, location), rumination, appraisals of the current situation and mood are collected after each “beep”. Previously, I operationalised reward experience as the *effect of minor events on positive affect*. ESM studies individuals prospectively and longitudinally, with short time delays between occurrence and assessment of experiences, minimising biases associated with selective forgetting, attributional style or knowledge about posterior events. I have ample experience with ESM; its validity and feasibility have been extensively documented by our group.

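### Sections 9.2 and 7.1.3 together allow, and read literally require, adjusting the primary randomised comparison for change in negative affect, a post-randomisation variable, with no unadjusted result beside it

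*Protocol*

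**What the plan says.** Section 9.2 of the protocol reads: "Analyses are corrected for possible confounders, thus only multivariate analyses will be used". It does not exempt the primary comparison of the randomised groups, and it leaves no room for an unadjusted one. Section 9.3 describes a two-level linear regression but names no covariates and no model terms.

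The only place where the protocol names variables of this kind is section 7.1.3, under the heading "Possible confounders/mediators". Two items are listed: "amount of rumination" and "baseline and change in negative affect". Nothing says which item is a confounder and which is a mediator.

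The timing follows from other sections. Section 7.2 states: "Randomization takes place after the baseline measurements and first week of ESM". Rumination is measured by questionnaire (RRS) at baseline. After the intervention both groups "again undergo the psychiatric interviews and the questionnaires" (section 7.3). It is also rated in the diary, where "rumination, appraisals of the current situation and mood are collected after each" signal (section 3, Experience Sampling Method).

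**The concern.** The primary objective (section 2) is whether reward experience can be changed experimentally. The quantity that answers it is the total effect of being randomised to MBCT. A variable measured after randomisation cannot confound that effect. If the training changes the variable, adjusting for it removes the part of the effect that runs through it. If unmeasured factors influence both that variable and reward experience, adjustment also adds collider bias, which can create an apparent effect where there is none.

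The protocol itself makes such a path plausible. It labels these variables possible mediators, and section 5.2 describes MBCT as reducing depressive symptoms. An analyst who follows 9.2 and 7.1.3 to the letter could report a diluted or distorted training effect. Because 9.2 admits only adjusted analyses, no second estimate would reveal it.

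**Working it through.** The plan gives no figure on this point. The 80% power in section 4.4 concerns the gene-by-training interaction and plays no part here. All path values below are assumptions, as is equal allocation (60 per arm), because the protocol gives only the total of 120.

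**Step 1: timing of each listed variable**

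| Variable in 7.1.3 | Time point | Safe as a covariate for the arm effect? |
|---|---|---|
| Baseline negative affect | Before randomisation | Yes |
| Change in negative affect | Needs the second ESM week, so after randomisation | No, if training changes it |
| Rumination | Not stated; measured before, after and at each signal | Only the pre-randomisation value |

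**Step 2: simple difference in means.** Let the total effect be 0.4 SD, let training lower negative affect by a SD, and let r be the size of the residual correlation between the two changes.

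Adjusted effect = 0.4 − a·r

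SE = √(2/60) · √(1 − r²) · √(1 + a²/4)

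- Unadjusted: SE = √(2/60) = 0.183, and power is 59%.
- a = 0.4, r = 0.3: effect 0.4 − 0.12 = 0.28, SE 0.178, power 35%. The loss is 0.12/0.4 = 30%.
- a = 0.6, r = 0.5: effect 0.4 − 0.30 = 0.10, SE 0.165, power 9%. The loss is 0.30/0.4 = 75%.

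**Step 3: simulation of the mechanism.** Each scenario uses 120 subjects, 4,000 runs, and subject-level regression with and without the post-randomisation variable M.

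| Assumed scenario | True total effect | Without M | Adjusted for M |
|---|---|---|---|
| Training does not change M | 0.40 | 0.40 | 0.40 |
| Half the effect runs through M | 0.40 | 0.39 | 0.20 |
| All of it runs through M | 0.40 | 0.40 | 0.00 |
| Half through M, plus an unmeasured common cause | 0.40 | 0.40 | 0.08 |
| No effect; training changes M; common cause | 0.00 | 0.00 | −0.13 |

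In the last row the rejection rate at a nominal 5% is 5.6% without M and 10.8% with it.

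**Step 4: the trial's own endpoint.** Section 7.1.1 defines the outcome as the increase in the effect of positive events on positive mood. In a multilevel model this is an arm × period × event coefficient, not a difference in means. Assume a true effect of 0.10 on the slope, equal to 0.4 of a slope SD of 0.25, with a = 0.6 and r = 0.5. Take 120 subjects and 45 valid signals per period.

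| How change in negative affect enters | Estimated training effect |
|---|---|
| Not at all | 0.100 |
| Main effect only | 0.099 |
| Main effect and its interaction with period | 0.100 |
| Event × period interaction added as well | 0.024 |

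A second simulation gave the same pattern: 0.096 unadjusted, 0.095 with a main effect, and 0.020 with the event × period interaction. Regressing each subject's change in slope on arm moved from 0.099 to 0.025 once change in negative affect was added. The closed form agrees: 0.10 − 0.6 × 0.5 × 0.25 = 0.025. The losses are 75% (0.099 to 0.025), 76% (0.100 to 0.024) and 79% (0.096 to 0.020).

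**The case against.** **The protocol does not write down the harmful model.** Section 9.2 speaks of confounders, whereas the 7.1.3 heading also covers mediators. Baseline negative affect may be meant as the confounder and its change as the mediator, with the covariate list left to a statistical analysis plan. This stands in part. A reader might infer that the primary effect will certainly be adjusted for change in negative affect, and the text does not go that far. But the point is not a missing detail: 9.2 states a rule for all analyses, 7.1.3 names the variable, and nothing separates the two roles. A later plan that follows both sections inherits the problem.

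**Change in negative affect may be a proper covariate elsewhere.** The secondary endpoint linking increase in reward experience to decrease in depressive symptoms (section 7.1.2) is not a randomised comparison, and change in negative affect could confound it. This stands, and the fix allows for it. It does not justify the adjustment in the arm comparison.

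**Rumination may be the baseline score.** This stands. A reader might infer that post-training rumination is certain to be adjusted for, but the protocol gives no time point, and the baseline score would do no harm.

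**An ordinary covariate hardly touches a slope endpoint.** This also stands. With only a main effect, the estimate in step 4 is essentially unchanged. The harm needs a change-score regression or an event × period term. The protocol specifies neither and excludes neither.

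**Conclusion.** The point holds in a conditional form. The two sections together permit, and read literally require, adjustment of the primary randomised comparison for a post-randomisation variable that the protocol itself calls a possible mediator, and they leave no unadjusted result for comparison.

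Bias arises only if MBCT changes negative affect and the covariate is allowed to act on the change in slope. Under the assumed paths (0.6 SD effect on negative affect, correlation 0.5) the estimate then loses about 75 to 80%. With a main effect alone, or if training leaves negative affect unchanged, it loses practically nothing.

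A reader might take the 30 to 75% loss, or the fall in power from 59% to between 9% and 35%, as properties of this trial. They are not. They illustrate a simple difference in means under assumed paths, and the 59% is not the power of the repeated-measures slope design. The size of any bias here cannot be worked out from the protocol.

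**What to change.** Replace the rule in section 9.2 with text along these lines:

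> The primary comparison of the randomised groups adjusts only for pre-specified variables measured before randomisation, such as baseline negative affect and baseline rumination. It is also reported without these covariates. Change in negative affect, and any rumination measured after baseline, are used only in separate mediation analyses or in the non-randomised secondary association between reward experience and depressive symptoms.

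In section 7.1.3, split the joint heading into baseline covariates and post-randomisation mediators, and give the measure and time point for rumination.

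The cost is a few sentences in two sections and one extra analysis. No new data are needed.

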### **9.3 Multivariate analysis**

ESM data have a hierarchical structure. Thus, multiple observations (level 1) were clustered within subjects (level 2). Multilevel analysis takes the variability associated with each level of nesting into account . The XT MIXED command in STATA 9.1 (Statacorp, College Station, Tex) was used to perform multilevel linear regression analyses.

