### ***Design***

Subjects are randomised to two groups. At baseline, all subjects will undergo a six-day period of ESM. Then, one group receives MBCT (8 weekly sessions of two hours including daily homework exercises) by an experienced MBCT therapist at the Community Mental Health Centre in Maastricht (CMHC) in addition to care as usual, and the other group only care as usual, followed by a second six-day ESM assessment. Any additional treatment, if applicable, will be kept constant within subjects. Subjects will be globally informed, but remain blind as to how ESM measures relate to testing the hypothesis.

[figure not shown]

\* Subjects are randomized in two groups. The only difference between these two groups is that the experimental group receives 8 weeks of MBCT training and the control group does not. Subjects of both groups continue with care as usual, if any.

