## 4. STUDY POPULATION

### 4.1 Population (base)

A sample of 120 depression-remitted subjects with residual symptomatology will be included, recruited from the CMHC in Maastricht, The Netherlands.

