### 4.4 Sample size calculation

A power simulation shows that for the least powerful analysis (gene-training effect interaction concerning the polymorphism with the most unequally divided genotypes), the power to detect interaction of small-moderate effect size (0.4) is still 80%. As I will use momentary assessment techniques yielding (6x10x2=) 120 different outcomes within each subject, a relatively small sample is needed for sufficient power to examine power-hungry gene-environment interactions

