## 7. METHODS

### 7.1 Study parameters/endpoints

#### 7.1.1 Main study parameter/endpoint

-The increase in reward experience in daily life, where reward experience is conceptualized as the effect of small positive daily life events on positive mood.

Since ESM is measures are performed 10 times a day for 6 days, there will be a maximum of 60 measurements within each subject concerning the effects of positive events on positive mood in the flow of daily life.

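### Section 9.3 fixes a two-level model and omits the day: this costs precision on the event slope and, if positive events cluster by day, can understate the standard error of the primary contrast

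*Protocol*

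**What the plan says.** Protocol section 9.3 describes the data as hierarchical and numbers the levels: "Thus, multiple observations (level 1) were clustered within subjects (level 2"). It adds, as a general remark with a textbook reference, "Multilevel analysis takes the variability associated with each level of nesting into account". It says nothing on a day level, an assessment-period level, random event slopes or the centring of the event variable.

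The sampling is described in section 3, under Experience Sampling Method: "Ten times a day on six consecutive days, the watch emits a signal at unpredictable moments between 7.30 a.m. and 10.30 p.m". This is done once before and once after the intervention, and section 4.4 writes the structure out as "6x10x2=) 120 different outcomes within each subject". Days and periods are thus factors in the protocol's own count.

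The main endpoint in section 7.1.1 is the increase in reward experience, where "reward experience is conceptualized as the effect of small positive daily life events on positive mood". Compared between arms, that is an event by time by group term. The planned size is 120 subjects (section 4.1) in two groups (section 3, Design).

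**The concern.** Reports from one day share that day's mood. Some days are good and some bad, beyond how a person differs from others. A model with observations directly within subjects counts this shared component as independent noise at each beep.

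Two things can follow. First, the slope is estimated with more noise than necessary, because part of the residual could have been removed. Second, if good-mood days are also days with more pleasant events, beeps carry less independent information on the slope than the model assumes, and its standard error is too small. Both bear on the primary endpoint, which is a difference in within-person slopes. They also bear on the gene and moderator analyses, for which section 4.4 relies on the many repeated measurements to justify a small sample.

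**Working it through.** **The plan's own figure.** Section 4.4 states that "the power to detect interaction of small-moderate effect size (0.4) is still 80" percent, for the gene by training interaction. This can be neither reproduced nor refuted: alpha, genotype split, variance components, dropout and the scale of 0.4 are not given. The point does not depend on it.

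**Inputs from the protocol.** D = 6 days per period, up to 10 beeps a day, 2 periods, 120 subjects, 2 arms (1:1 assumed).

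**Assumed, because the protocol gives no value.** Valid beeps per day m = 5-9; day share of within-person variance ρy = 0.1-0.3 for positive affect and ρx = 0.05-0.2 for events.

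**Step 1: one person-week, closed form.** Scale the within-person variance of affect and of events to 1 each. The expected sums of squares of the event score are

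- between days: B = (D − 1)(1 − ρx + mρx)
- within days: W = D(m − 1)(1 − ρx)

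The slope variances are

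- without the day, as the model reports it: 1/(B + W)
- without the day, true: [W(1 − ρy) + B(1 − ρy + mρy)]/(B + W)²
- with a day intercept: 1/[W/(1 − ρy) + B/(1 − ρy + mρy)]

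Example with m = 7, ρx = 0.2, ρy = 0.3: B = 5 × 2.2 = 11 and W = 36 × 0.8 = 28.8.

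- Reported: 1/39.8 = 0.02513.
- True: (28.8 × 0.7 + 11 × 2.8)/39.8² = 50.96/1584.04 = 0.03217.
- SE ratio, true to reported: √(0.03217/0.02513) = 1.13. The nominal 5% test rejects 2Φ(−1.96/1.132) = 8.3%.
- With the day intercept: 1/(28.8/0.7 + 11/2.8) = 0.02219, which is 31% below 0.03217.

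| m | ρx | ρy | true SE / reported SE | rejection at 5% | variance cut by day intercept |
|---|---|---|---|---|---|
| 5 | 0 | 0.1 | 0.99 | 4.8% | 3% |
| 9 | 0 | 0.3 | 0.98 | 4.5% | 21% |
| 5 | 0.05 | 0.1 | 1.00 | 5.0% | 3% |
| 7 | 0.2 | 0.3 | 1.13 | 8.3% | 31% |
| 9 | 0.2 | 0.3 | 1.18 | 9.6% | 37% |

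If the reported variance uses the residual mean square net of the week's mean, the ratio is exactly 1.00 at ρx = 0 and reaches 1.20 (10.3%) in the last row. A simulation of the full arm by week contrast (60 per arm, 1500 runs) gave 7.1% at shares 0.2/0.2. The closed form gives 6.4-8.0% there for m = 5-9.

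**Step 2: the primary contrast.** For 120 subjects × 2 periods × 6 days × 10 beeps, I compared the model SE of event by time by group with its true (sandwich) SE. Assumed: subject variance 30% of total, day variance 5-10% of total (5/70 = 7% to 10/70 = 14% of within-person variance), subject slope SD 0.1, and no slope variation between periods.

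| event score | day share of events | model SE / true SE, two levels | type I error |
|---|---|---|---|
| raw | 0.1-0.3 | 0.93-0.81 | 7-11% |
| person-centred | 0.1-0.3 | 0.98-0.87 | 6-9% |
| person-centred | 0 | 1.00-1.01 | about 5% |
| day-centred | 0 or 0.3 | 1.035-1.07 | 4.3-3.5% |

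With a random day intercept the ratio is 1.00 in every row. The true SE of the two-level estimate exceeds that of the day model by 0-12%, and by nothing when the score is day-centred.

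**Step 3: is the day intercept enough?** Let the event slope also vary by subject-period with SD 0.1 (a subject-by-period intercept variance of 5% was switched on in the same runs). The two-level ratio is then 0.55-0.89. Adding only the day intercept leaves it at 0.71-0.82, a type I error of 11-17%. For day-centred events, which a period intercept cannot distort, it is still 0.75-0.82, so the slope variation alone suffices to cause the problem.

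**The case against.** The strongest reply is that section 9.3 is a short description, and that random-effects details belong in a statistical analysis plan, which is not shown. That holds for random slopes, residual correlation and centring: silence on these is no error in itself. It does not hold for the levels, which section 9.3 counts and numbers as two. It is also fair that the sentence about each level of nesting is a general remark and not a promise that the section then breaks. The point rests on the numbered levels set against the sampling scheme.

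A reader might infer that leaving out the day always understates the standard error and so inflates false positives. The documents do not support that. The direction depends on whether positive events cluster by day and on how the event score is centred, and the protocol states neither. Without day clustering of events the SE is about right, and with day-centring it is 3.5-7% too large in Step 2. For the plain event slope, as opposed to the three-way contrast, the two-level ratio in Step 2 stays within 0.945-1.025.

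A reader might also infer that a day intercept would by itself make the primary test valid. Step 3 shows that it would not if slopes vary between periods. Nor can one conclude that the stated 80% power is wrong, since its inputs are not given.

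**Conclusion.** The point holds in this form. The stated two-level model omits a level that the design contains. The loss of precision on the event slope arises whenever affect varies by day and the event score is not day-centred: 3-37% of the slope variance for an affect day share of 0.1-0.3 and an event day share of 0.05-0.2, and still 3-21% if events do not cluster by day at all. An understated standard error for the primary contrast is possible but conditional. It needs events that cluster by day, and it then puts the type I error at roughly 5-10% under the same shares. Every size here rests on assumed variance shares, so the omission is certain and its effect in this trial is not. It is worth correcting because the primary endpoint is a within-person slope and the change costs almost nothing.

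**What to change.** Rewrite section 9.3 as beeps (level 1) within days (level 2) within subjects (level 3), with a random intercept for each day of each assessment period. Use this model for the primary contrast and for the gene and moderator analyses.

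In the same edit:

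- state how the event variable is centred (raw, within person or within day);
- let the event slope vary by subject and by subject-period, or use standard errors clustered by subject.

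The second item is needed because the day intercept alone leaves the primary test invalid when slopes vary. The change takes a few sentences and extra random terms in the mixed model already planned, with no new data or subjects. The price is a slightly more complex model that may converge more slowly.

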**Objective:**

- 1) Can the ability to experience reward in daily life be experimentally modified?
- 2) How does experimental modification of reward impact on depressive symptomatology and can individual variation be traced to genetic variation.

**Study design:** An intervention study is used in which subjects are randomized to treatment as usual (TAU) or TAU + mindfulness-based cognitive therapy. Experience Sampling Method (ESM) is a structured diary, momentary assessment technique to study subjects in their daily life. Before and after the intervention subjects undergo a six-day period of ESM assessment. Subjects will be globally informed, but remain blind as to how ESM measures relate to testing the hypothesis.

**Study population:** A sample of 120 depression-remitted adult subjects with residual symptomatology (Ham-17>7) recruited from the community mental health centre in Maastricht (CMHC).

**Intervention (if applicable):** The experimental group receives 8 weeks of mindfulness training by an experienced trainer in addition to their normal treatment, if any. Sessions are weekly (2,5 hours a session) and subjects receive daily homework exercises. The control group continues their normal treatment, if any.

**Main study parameters/endpoints:** The increase in reward experience in daily life, whereby reward experience is conceptualised as the effect of small daily life positive events on positive mood state. Since ESM measurements are performed 10 times a day for 6 days, there will be a maximum of 60 measurements within each subject concerning effects of positive events on positive mood state in the flow of daily life.

**Nature and extent of the burden and risks associated with participation, benefit and group relatedness:** There are no health risks associated with participation. There is a personal benefit for subjects in that they are randomized to receive an extra training that is expected to improve their resilience against depression. Time investment for subjects is 2,5 hours for questionnaires (distributed over three meetings, including the screening). In addition, they participate twice in the ESM protocol (6-day period of filling in dairies concerning daily life events and mood). Before the start each ESM protocol they have to come for a short meeting (15 -30 min) to receive specific instructions related to this

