**10.6 Incentives (if applicable)**

Subjects will receive free MBCT training. Subjects that are randomized to enter the control group are offered an MBCT course that they can follow later, after the study. In addition, they receive some financial compensation in relation to the amount of time they invested in the study, with a maximum of 50 euro. In addition, subjects are fully compensated for any travel costs related to the study.

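### If MBCT is taught in shared courses, the two-level model in section 9.3 leaves out a level in one arm and understates the standard error of the primary training effect

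*Protocol*

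**What the plan says.** Section 9.3 gives the structure of the analysis model as "multiple observations (level 1) were clustered within subjects (level 2" and says that Stata's mixed-model command "was used to perform multilevel linear regression analyses". It justifies this on the ground that "Multilevel analysis takes the variability associated with each level of nesting into account". No course, group or trainer level appears there, and section 4.4 (sample size) does not mention one.

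On delivery, the Summary says "The experimental group receives 8 weeks of mindfulness training by an experienced trainer". Section 3 (Design) says "one group receives MBCT (8 weekly sessions of two hours including daily homework exercises) by an experienced MBCT therapist" and places this at one mental health centre. The control arm has usual care only. Section 10.6 adds: "Subjects that are randomized to enter the control group are offered an MBCT course that they can follow later, after the study".

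No section says whether sessions are held in groups, how many subjects share a course, how many courses are run, or how many trainers take part.

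**The concern.** Subjects are randomised individually. If the experimental subjects are then trained together, those in one course share its sessions, calendar period and co-participants, and their changes in reward experience are likely to be correlated. Controls have no such grouping. That is a partially nested design, with clusters in one arm only.

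The primary objective asks whether training changes reward experience, so the key contrast is between subjects. A model that stops at the subject treats all MBCT subjects as independent. A subject-level random slope for events does not absorb variation between courses, and neither do more beeps per subject. The confidence interval would be too narrow, and one unusually good or poor course could be read as a general effect of MBCT. By section 9.3's own principle, a level of nesting that exists should be in the model.

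**Working it through.** **Is sharing likely?** Total sample 120 (section 4.1). The allocation ratio is not stated, so 1:1 is assumed, giving 60 per arm. There are eight weekly sessions. Section 3 gives their length as two hours, while the Summary and section 7.3 give two and a half; these passages need reconciling, and both are used here.
- Hours per subject: 8 × 2 = 16, or 8 × 2.5 = 20.
- One-to-one trainer hours: 60 × 16 = 960, or 60 × 20 = 1,200, and up to twice that if controls take the later course.

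Together with the word 'course' in section 10.6, and the account in section 5.2 of training by attention exercises, this makes shared sessions a reasonable inference. It remains an inference.

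**The plan's own figure.** The only stated power is 80% for a gene-by-training interaction of 0.4 (section 4.4). It does not concern the primary contrast. It cannot be reproduced, because alpha, sidedness, genotype frequencies, variance components, the unit of 0.4 and the drop-out rate are not given. It is not used below.

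**Size of the understatement.** Let m be subjects per course and ρ the course ICC of the subject-level change in event slope. Neither is in the protocol, so ranges are shown. With total variance 1 in each arm:
- Variance assumed by the subject-level test: 1/60 + 1/60.
- Actual variance: [1 + (m − 1)ρ]/60 + 1/60.
- Ratio of true to reported standard error: r = √{([1 + (m − 1)ρ] + 1)/2}.
- True two-sided error rate at nominal 5%: 2{1 − Φ(1.96/r)}.

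Example, m = 10 and ρ = 0.05: 1 + 9 × 0.05 = 1.45; (1.45 + 1)/2 = 1.225; r = 1.107; error rate 2{1 − Φ(1.96/1.107)} = 7.7%.

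| ICC | m = 6 | m = 10 | m = 12 | m = 15 |
|---|---|---|---|---|
| 0 | r 1.00, 5.0% | 1.00, 5.0% | 1.00, 5.0% | 1.00, 5.0% |
| 0.01 | 1.01, 5.3% | 1.02, 5.5% | 1.03, 5.6% | 1.03, 5.8% |
| 0.02 | 1.02, 5.6% | 1.04, 6.0% | 1.05, 6.3% | 1.07, 6.6% |
| 0.05 | 1.06, 6.5% | 1.11, 7.7% | 1.13, 8.3% | 1.16, 9.2% |
| 0.10 | 1.12, 8.0% | 1.20, 10.4% | 1.25, 11.5% | 1.30, 13.3% |

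**Check by simulation** (40,000 trials per setting, person-level outcome). For m = 6, 10, 12 and 15, the subject-level t-test gave 6.4%, 7.9%, 8.4% and 9.2% at ICC 0.05, and 8.1%, 10.4%, 11.5% and 13.3% at ICC 0.10. At ICC 0 it gave 4.9-5.1%. A test of course means against individual controls, with Satterthwaite degrees of freedom, gave 5.0-5.8% at ICC 0.05 and 5.1-6.0% at ICC 0.10.

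**Number of courses.** 60/15 = 4 to 60/6 = 10.

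**The case against.** The strongest objection is that the premise is not written down. No section mentions groups or co-participants, and 'course' may mean only a series of sessions. The trainer-hours figure would exclude one-to-one teaching only with a staffing limit or time window, and the protocol gives neither. This stands, and it makes the point conditional.

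The size is also assumed throughout. At ICC 0.01 the effect is negligible, and because the outcome is a change in an estimated slope, estimation error dilutes any course ICC. The calculation uses a person-level outcome, not the full event-slope model. These points stand too, and are why a range is given.

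It may further be said that section 9.3 only describes the diary data, and that a therapy-group term belongs in an analysis plan not shown. This stands in part: such a plan could add the level. But the protocol does state a hierarchy, and it stops at the subject.

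Three stronger readings are tempting and should not be adopted:
- *One trainer makes the standard error too small.* The documents use the singular but never say that one person gives all the training. If one did, the trainer effect would be confounded with the MBCT arm. That limits generalisability and cannot be modelled, but it does not shrink the standard error. Only variation between courses, or between several trainers, does.
- *Objective iii is affected in the same way.* Genotype varies within a course, so a shared course effect largely cancels from the gene-by-training interaction. Simulation with 60 per arm, courses of 6, 12 or 15, ICC 0.05 or 0.10 and genotype frequency 0.1, 0.25 or 0.5 (8,000 trials in each of 18 settings) gave false-positive rates of 4.6-5.4%.
- *The present analysis overstates power by 6 to 20 points.* At ICC 0.05 that gap sets a subject-level test whose true error rate is 6.5-9.2% beside a valid test near 5%, so it mixes error inflation with lost precision.

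**Conclusion.** The point holds conditionally. The model as written treats MBCT subjects as independent. If they share courses and the course ICC is above 0, the standard error of the primary training contrast is too small: by about 2-7% of the reported value at ICC 0.02, 6-16% at 0.05 and 12-30% at 0.10. The corresponding false-positive rates are about 5.5-7%, 6-9% and 8-13%. With individual training or zero ICC nothing is lost.

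The result rests on 60 per arm, courses of 6 to 15, clustering in the MBCT arm only and equal total variance in the two arms. A reader might infer that the protocol documents group teaching and that the interval is therefore certainly too narrow. It documents neither; it leaves the format unstated and specifies a model that is right only if subjects are independent.

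**What to change.** 1. State in sections 3 and 5.2 whether MBCT is given in groups and, if so, the intended course size.
2. Record the course (start cohort) of every experimental subject when training begins.
3. Where sessions are shared, amend section 9.3 to a partially nested model: beeps within subjects, and subjects within course in the MBCT arm only, with each control as its own cluster. Put the course random effect on the change in event slope, test the training effect with Satterthwaite or Kenward-Roger type degrees of freedom, and report the course ICC.
4. If the course variance cannot be estimated with so few courses, report a sensitivity analysis over plausible ICCs instead.

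The cost is one variable and a few sentences, with no extra patients or visits. The downside is a wider interval on few course-level degrees of freedom (about 4 to 10 courses). Clustering itself also costs power, whichever model is fitted. An effect with 80% power under independence has, before any loss for degrees of freedom, Φ(2.80/r − 1.96). For courses of 12 at ICC 0.05 that is Φ(2.80/1.129 − 1.96) = 70%, and restoring 80% would take about 1.28 times the sample. The amended model makes that loss visible; it does not create it.
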